## Abstract

**Background:**

Graded health benefits of physical activity have been demonstrated for the reduction of coronary heart disease, some cancers, and type-2 diabetes, and for injury reduction and improvements in mental health. Older adults are particularly at risk of physical inactivity, and would greatly benefit from successful targeted physical activity interventions.

**Methods/Design:**

The Healthy Steps study is a 12-month randomized controlled trial comparing the efficacy of a pedometer-based Green Prescription with the conventional time-based Green Prescription in increasing and maintaining physical activity levels in low-active adults over 65 years of age. The Green Prescription interventions involve a primary care physical activity prescription with 3 follow-up telephone counselling sessions delivered by trained physical activity counsellors over 3 months. Those in the pedometer group received a pedometer and counselling based around increasing steps that can be monitored on the pedometer, while those in the standard Green Prescription group received counselling using time-based goals. Baseline, 3 month (end of intervention), and 12 month measures were assessed in face-to-face home visits with outcomes measures being physical activity (Auckland Heart Study Physical Activity Questionnaire), quality of life (SF-36 and EQ-5D), depressive symptoms (Geriatric Depression Scale), blood pressure, weight status, functional status (gait speed, chair stands, and tandem balance test) and falls and adverse events (self-report). Utilisation of health services was assessed for the economic evaluation carried out alongside this trial. As well, a process evaluation of the interventions and an examination of barriers and motives for physical activity in the sample were conducted. The perceptions of primary care physicians in relation to delivering physical activity counselling were also assessed.

**Discussion:**

The findings from the Healthy Steps trial are due in late 2009. If successful in improving physical activity in older adults, the pedometer-based Green Prescription could assist in reducing utilisation of health services and improve cardiovascular health and reduction of risk for a range of non-communicable lifestyles diseases.

**Trial registration:**

Australian and New Zealand Clinical Trials Registry ACTRN012606000023550

## Background

Many older adults are at risk of lifestyle-related diseases because of a lack of regular physical activity. Physical inactivity has both direct and indirect costs to the health of the population. Evidence shows the graded health benefits of physical activity for the reduction of coronary heart disease, some cancers, type-2 diabetes, obesity, osteoporosis, and injury (including falls in the elderly) [1]. Physical activity participation by older adults can also improve quality of life and physical and psychological function (including depression), facilitate independent living, and reduce the risk of dementia [2-5]. Improved physical and psychological functioning through regular physical activity also results in overall improved quality of life in older adults [6]. Older adults are particularly at risk of inactivity [7], and they also contribute disproportionately to the burden on health care systems [8].

The Green Prescription is a current successful strategy to deliver physical activity advice in New Zealand [9,10]. It is an activity-based prescription program administered through Primary Care settings with the support of trained telephone counselors. The Green Prescription is based around achieving daily time-based activity goals on the basis of the US Surgeon General's recommendation, and the national physical activity guidelines of 30 minutes of moderate activity on most, if not all, days of the week. The program is efficacious in increasing and maintaining physical activity 12 months post prescription [9] and is cost-effective both in terms of relative cost per quality adjusted life year [11] and per successful treatment [12].

Research has also shown that incidental physical activity may be an important contributor to achieving health benefits, especially for older adults [13]. Pedometer-based interventions have been suggested as an effective way to maintain levels of activity conducive to health benefits, especially in older adults (as evidenced in a systematic review) [14]. Further, using a pedometer to monitor the accumulation of daily physical activity may be a superior motivation and adherence tool to time-based goal setting.

In this study we aimed to compare the efficacy of a pedometer-based Green Prescription with the conventional time-based Green Prescription in increasing and maintaining physical activity levels in low-active older adults. As well, the trial sought to examine the effects of the interventions on health-related quality of life, functional status, blood pressure, weight status, and health care utilisation and costs. Incremental cost-effectiveness and cost-utility ratios will also be estimated.

## Methods/Design

### Design

A randomized controlled trial design was used to investigate the efficacy and cost-effectiveness of a pedometer-based Green Prescription in improving physical activity levels and health outcomes in low active older adults compared with the usual (time-based) Green Prescription. Ethical approval to conduct the study has been granted by the Health and Disability Ethics Committees, Northern Y Regional Ethics Committee (Reference Number NTY/05/11/086).

### Participants

Participants were community dwelling adults aged 65 years and older living on the North Shore in Auckland, New Zealand, who were identified through their usual primary care physician's computer databases. Participants were eligible for inclusion in the trial if they were low-active (i.e., had not engaged in at least 150 minutes of moderate physical activity accumulated over at least 5 days in the previous week). Other inclusion criteria were being able to freely give informed consent, being able to communicate in English, ability to walk, and having no health conditions that contraindicate physical activity participation as judged by their general practitioner (primary care physician). Exclusion criteria were visual impairment to a level where a pedometer screen could not be read.

### Recruitment (see Figure 1)

**Figure 1 F1:**
[figure not shown]
**Recruitment Flowchart and Identification of Eligible Population**.

Recruitment was modelled on that used in other primary care physical activity interventions for older adults [15,16]. A sample of 17 general practitioners from 10 medical practices on the North Shore of Auckland, New Zealand, accepted a faxed invitation to be involved in the study. These 10 practices (out of 38 that were initially invited) covered a range of socio-economic areas of this region of Auckland. The invitation was followed up with a telephone call to the general practitioners and a visit by one of the study staff. On agreement, a list of all patients 65 years and older was generated and the general practitioners and practice staff excluded patients who had a medical condition that would not allow safe participation in a physical activity program, dementia, and those who were not community-dwelling. An invitation letter, signed by the general practitioner, was mailed to patients with a reply-paid response card addressed to the research team. Those who returned their card indicating interest in the study were contacted by telephone to explain the study further and were screened for physical activity level with the question "As a rule, do you do at least half an hour of moderate or vigorous exercise (such as walking or a sport) on five or more days a week?" The positive predictive value of this question is 81% when identifying "less active" adults [9]. Health conditions contraindicated to physical activity were also screened using the Physical Activity Readiness Questionnaire (PAR-Q) [17]. This instrument is validated as an assessment tool for screening readiness for prescription of exercise, and is seen as appropriate for older adults. This tool was included to maximise participant safety. If the participant met the PAR-Q criteria, and was considered insufficiently active, the Research Officer arranged a home visit. If the patient had any contraindications to physical activity, general practitioner clearance was sought. Potential participants who were sufficiently active for health gain and/or who did not gain general practitioner clearance were excluded from participation in the trial. Patients who did not return their response card within three weeks were followed up with a single telephone call from the office of the general practitioner by the Research Officer to ascertain their willingness to participate in the study.

After making suitable arrangements, the Research Officer visited the patient in their home to answer any additional questions on the study, provide the information sheet, obtain informed consent, book a general practitioner appointment for commencement of the intervention, provide a falls and injuries calendar and reply-paid envelopes, and then take the following baseline measures: demographics questionnaire, blood pressure and current blood pressure medications (if applicable), lower extremity function measures, quality of life, physical activity, depressive symptoms, and self-reported health status.

During the general practitioner visit, the patient was randomized into either the standard Green Prescription or the pedometer Green Prescription group and commenced on the intervention through the initial prescription of physical activity. Those in the pedometer group were issued with a pedometer by the general practitioner or practice nurse and instructed in its use. At the end of the appointment the Green Prescription was faxed to the local Regional Sports Trust for continuation of the intervention. The Regional Sports Trust is as government-funded organization involved in provision of sports and physical activity opportunities and programs for the population of that region. General practitioners and other relevant practice staff participated in training relating to the administration of the intervention.

Recruitment was undertaken over 17 months from July 2006 to December 2007 to allow for the interventions to be delivered during all seasons. A total of 330 people were recruited into the trial. At 3 months, 278 remained in the study with 270 remaining at 12 months. Included in the 330 recruited participants were 31 couples (defined as living in the same household). In order to reduce the effects of contamination both individuals in the couple were allocated to the same intervention and were treated as clusters for the purposes of statistical analysis.

### Randomisation and Blinding

Randomisation was blocked and lists generated by an independent statistician ([name]) using specialist computer software. This list was used to allocate each participant to either the standard Green Prescription or pedometer Green Prescription group after enrolment in the study at the home visit. The allocation was advised to the general practitioner via a telephone call (from a Research Officer) to their reception staff before the participant attended their consultation for prescription of physical activity.

### Intervention Group

Participants in the pedometer Green Prescription group were provided with an initial prescription for physical activity by the general practitioner that was then followed up by 3 telephone counselling sessions by a physical activity counsellor at the Regional Sports Trust over a 3-month period (i.e., one call per month). The telephone counselling was based within a framework of the transtheoretical model of behaviour change [18] and used the principals of motivational interviewing [19] such as assisting patients to identify barriers and solutions to physical activity participation, and discussing positive aspects of participation in activity and negative aspects of not participating in enough activity. The strategies used were aimed at increasing participation in a variety of physical activities with an emphasis on walking. Goal setting was used as an important component of the intervention and participants were encouraged to increase their participation in activity by monitoring the number of steps recorded by their pedometer. In this way, the pedometer was used to provide immediate feedback to the participants regarding their accumulation of activity towards daily goals.

The content of each telephone counselling call was specific to each participant but typically included the following:

• Call 1 - Introductory call, information provision and goal setting (15-30 minutes).

• Call 2 - Follow-up call to assess progress (10-15 minutes).

• Call 3 - Final call to provide encouragement and relapse prevention (10-15 minutes).

### Control Group

Participants in the standard Green Prescription group participated in the same initial activity prescription by the general practitioner and the 3 telephone counselling sessions provided by the Regional Sports Trust with one difference: the physical activity prescription and counselling were based around accumulating activity in the context of time-related goals as opposed to pedometer step-related goals.

### Outcome Measures

Outcome measures were assessed at baseline, 3 months (end of intervention), and 12 months during home visits by the Research Officer at these times. All questionnaires were provided in English language only. The following were used.

#### Demographics

Demographics were collected at baseline and included self-identified ethnicity (allowing multiple ethnic groups), age, sex, marital status, education, occupation (lifetime and present), home ownership, and telephone and car ownership or access.

#### Physical activity

The Auckland Heart Study Physical Activity Questionnaire (AHSPAQ) was used to measure physical activity. The AHSPAQ is a validated [20] self-report questionnaire suitable for use with less active adults in primary care [21]. The AHSPAQ allows calculation of energy expenditure of leisure, occupational and domestic activity, rest, and sleep according to a standard physical activity compendium for energy expenditure values [22]. Software for the analysis of the AHSPAQ has been developed to calculate total and component energy expenditure, as well as duration-based physical activity outcomes [23].

Amount of walking on the previous day was assessed with a series of questions that requested participants to indicate the number of minutes they walked in 4 segments of the day: before breakfast, between breakfast and lunch, between lunch and dinner, and after dinner.

#### Quality of life

The SF-36 is a validated measure of health-related quality of life [24]. It assesses both mental health and physical health along eight dimensions; physical functioning, role physical, bodily pain, general health, vitality, social functioning, role emotional, and mental health. The SF-36 has been validated on New Zealand populations [25], has demonstrated suitability for use in elderly populations [26], and is associated with the stage of motivational readiness to changes in physical activity [27].

#### Functional status

Lower extremity function measures from the Short Physical Performance Battery (SPPB) (gait speed, chair stands, and tandem balance test) were used as a measure of functional capacity and disability risk [28-30].

#### Depressive symptoms

The Geriatric Depression Scale (GDS-15) is a well validated and extensively used scale [31] and was used to measure depressive symptoms in the Healthy Steps trial.

#### Blood pressure

Repeated blood pressures were measured and blood pressure medications were recorded.

#### Height and weight

Height was measured with a standard portable stadiometer, and weight was measured with digital scales. Body mass Index was calculated from height and weight.

#### Adverse events and associated costs

As a monitor of adverse events, all participants were monitored for one year using standardised reporting forms in the form of fridge diaries. These were 12-month diaries, (one page per month) that were filled in whenever a participant had a fall, injury, or musculoskeletal problem. All hospitalisations, bruises, skin lacerations, sutures, fractures, X-rays, and admissions as a result of these problems were also recorded on the falls form. As well, patient fees for general practitioner visits, consults with other health professionals, and costs associated with physical activity participation were collected on these forms for the economic evaluation. Forms were mailed to the research team monthly and a Research Officer telephoned the participant to follow-up on any injuries recorded and to prompt participants who had failed to send in their forms.

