#### Use of healthcare services

Summary information on the use of general practitioner services and inpatient hospital care, from general practitioner and New Zealand Health Information Service records, were obtained for the year prior to intervention and compared with the year following intervention delivery. Use of all other health services and any personal costs associated with the physical activity regime were collected on the monthly diaries described above.

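### The only adverse event capture described is triggered by self-reported falls, injuries and musculoskeletal problems, so other medical admissions and deaths are not captured as harm, although inpatient and practice records are obtained

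*Protocol article*

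**What the plan says.** Adverse event capture is described in one place, the section Adverse events and associated costs. It opens: "As a monitor of adverse events, all participants were monitored for one year using standardised reporting forms in the form of fridge diaries". The forms are "filled in whenever a participant had a fall, injury, or musculoskeletal problem". The hospital-related items are listed as "All hospitalisations, bruises, skin lacerations, sutures, fractures, X-rays, and admissions as a result of these problems", and the form that receives them is called the falls form. Follow-up is by telephone: "a Research Officer telephoned the participant to follow-up on any injuries recorded and to prompt participants who had failed to send in their forms". The Abstract (Methods/Design) gives self-report as the source, ending its list of outcome measures with "falls and adverse events (self-report".

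A separate section, Use of healthcare services, obtains "Summary information on the use of general practitioner services and inpatient hospital care" from practice and national health information records. These records cover the year before the intervention and the year after it was delivered, and their stated purpose is to compare use between the two periods. No section links them to adverse events, and none names deaths or cardiovascular events as harm outcomes.

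Safety at entry is treated more broadly. Practices removed patients whose condition made participation unsafe, and the rest were screened with the PAR-Q. "If the patient had any contraindications to physical activity, general practitioner clearance was sought", and those not cleared were excluded.

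**The concern.** The article is not silent on how adverse events are captured. It states the instrument, the trigger, the source and the follow-up, and the trigger is narrower than the term adverse events suggests. It suits falls and injuries well. It gives no reason to make an entry for a heart attack, a stroke or any other medical admission that did not arise from a fall, injury or musculoskeletal problem, and a death cannot be self-reported.

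What is at stake is the safety statement the trial can support. If the report says that adverse events were similar in the two groups, readers will take that to cover serious medical events and deaths, when the measure behind it covers three kinds of problem. Both groups receive an activity prescription, so the gap also affects the description of harm overall, not just the comparison of groups. The article recognises a wider safety question at entry, through the PAR-Q and the practitioner's clearance, but the follow-up it describes does not match that breadth.

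**Working it through.** The plan gives no event rate and no power statement for harm, so there is no figure to reproduce. The main check is of the text. A short calculation then gives the scale.

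**1. Which events reach the adverse event record**

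| Event in the year | Meets the diary trigger? | Where it would appear as written |
|---|---|---|
| Fall, injury, musculoskeletal problem | Yes | Adverse event form |
| Admission caused by one of these | Yes | Adverse event form |
| Cardiac, stroke or other medical admission | No | Inpatient records, as service use |
| Death | No, and cannot be self-reported | No harm outcome is stated |

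The second row depends on how the hospital items are read. Their opening words could be taken to mean every hospitalisation. But the sentence limits them: "admissions as a result of these problems were also recorded on the falls form". Both the limiting phrase and the name of the form favour the restricted reading.

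**2. What the records already offer**

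Inpatient and practice records do not depend on a participant returning a form. Three features bear on using them for harm:

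- They are described as summary information, so cause and date of admission may not be included.
- Their follow-up window is the year after the intervention was delivered. That could start at the prescription visit or after the three months of counselling. On the second reading, admissions during the counselling period fall in neither comparison year.
- Their only stated use is service use, which feeds the economic evaluation.

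**3. Scale, on assumed rates**

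Inputs: 330 participants recruited (Recruitment); 165 planned per group (Sample Size); an assumed annual rate r of cardiovascular event or death of 1% to 5%. The calculation treats participants as independent and so ignores the 31 couples.

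- Expected events, 330 × r: 330 × 0.01 = 3.3 and 330 × 0.05 = 16.5, so about 3 to 17.
- Chance of at least one event, 1 − (1 − r)^330: at r = 0.01 this is 1 − 0.99^330 = 0.964, and it is higher at every larger rate.
- Power to detect a doubling (r against 2r, 165 per group, two-sided 5%) = Φ[(r − 1.96 × √(2p̄(1 − p̄)/165)) / √((r(1 − r) + 2r(1 − 2r))/165)], with p̄ = 1.5r:
  - r = 0.01: (0.01 − 1.96 × 0.01338) / 0.01337 = −1.21, so power is 0.11.
  - r = 0.05: (0.05 − 1.96 × 0.02900) / 0.02887 = −0.24, so power is 0.41.

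On these assumptions some such events are very likely, but a formal comparison of groups would be uninformative. The right output is a descriptive table.

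**The case against.** The strongest reply is that the diary is one instrument and is not claimed to be the whole safety procedure. This is a condensed article. Reporting of serious events and deaths is commonly left to the full protocol, and nowhere does the article say that such events are excluded. That is a fair limit: the exclusion is inferred from the trigger, and a wider procedure may exist. It does not dispose of the point, because the article does set out how adverse events are monitored, and the rule it states is narrow.

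Three stronger readings are tempting, and the documents do not support them.

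- *A reader might infer that a group difference in admissions would go unexamined.* Health care utilisation is among the effects the trial sets out to study (end of Background), and inpatient use is compared under Use of healthcare services. What is missing is the treatment of these events as harm and any split by cause.
- *A reader might infer that diary events are lost for people who left.* The numbers remaining imply 330 − 278 = 52 (15.8%) gone by 3 months and 330 − 270 = 60 (18.2%) by 12 months. But the article says that all participants were monitored for one year, with telephone prompts for missing forms. It does not say that diaries stopped on leaving, and it gives no reasons for leaving.
- *A reader might infer that a definite number of serious events is missed.* Any count rests on an assumed rate.

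It is also fair to say that entry screening lowers the risk, and that the groups differ only in step-based against time-based goals. Both make a large difference in serious events between groups less likely. Neither removes the need to report such events.

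**Conclusion.** The point holds in a limited form. The adverse event capture described in the article covers self-reported falls, injuries and musculoskeletal problems, and admissions that result from them. Other medical admissions and deaths are not captured as harm, while records that could supply at least the admissions are obtained and assigned only to service use.

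The size cannot be taken from the documents. At an assumed 1% to 5% a year it would be about 3 to 17 events among 330 participants, with power of about 11% to 41% for a doubling. The gain from closing the gap is therefore a complete description of harm, not a test. The conclusion rests on the restricted reading of the hospital items and on the article being the only description at hand. The comparison of physical activity is unaffected. The change should be made because it is cheap and because, without it, a statement about adverse events would leave out the most serious ones.

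**What to change.** In Adverse events and associated costs, state that all-cause admissions, cardiovascular admissions where the extract gives cause, and deaths, from randomisation to 12 months, are taken from the inpatient and practice records described under Use of healthcare services. State that they are reported descriptively by allocated group for all randomised participants, where consent allows, beside the diary-based falls and injuries, with no formal test between groups.

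The output is one safety table, with no new visits or procedures. The cost lies in the extract. It must carry cause and date of admission, record deaths, and run from randomisation, not from an unspecified point after the intervention was delivered. Recruitment has closed and the measurements are described in the past tense, so this may mean a further retrospective extract within existing consent. The analysis is still described as to come, so the change can be made before reporting. If cause is not available, all-cause admissions and deaths should still be reported, with that limit stated. If the full protocol already has a wider procedure, a sentence pointing to it, together with the same table, would settle the point.
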